# TaIlored ManagEment of Sleep (TIMES) for people with dementia and mild cognitive impairment in primary care in England: protocol for a feasibility cluster-randomised controlled trial

**DOI:** 10.1186/s40814-026-01791-0

**Published:** 2026-03-07

**Keywords:** Sleep disturbance, Clinical trial, Complex intervention, Primary healthcare, Decision support tool, Tailored care, Dementia, Mild cognitive impairment

## Abstract

**Background:**

People living with dementia (PLWD) and mild cognitive impairment (MCI), and their family carers, often experience sleep disturbance which can impair daily living and care. There are limited options for effective long-term pharmacological management of sleep disturbance, yet recent advances in non-pharmacological approaches offer promising alternatives. TIMES is a novel, complex intervention, which aims to improve wellbeing for PLWD/MCI and their carers in primary care, by developing whole-person, tailored care plans that optimise management of sleep disturbance in context.

**Methods:**

Two-arm cluster-randomised (1:1), single-blinded, feasibility trial in 10 general practice sites in England, recruiting 64 patient–carer dyad participants (32 intervention + 32 treatment as usual). Co-primary objectives are to assess the feasibility and acceptability of conducting a subsequent definitive cluster-randomised controlled trial (cRCT) of the TIMES intervention. Secondary objectives include assessing the ability to collect data to address putative primary and secondary outcomes of a definitive cRCT. We will collect participant demographics at screening, and the following outcome measures at baseline, 9 and 15 week follow-ups: Sleep Disorders Inventory (SDI); Epworth Sleepiness Scale (ESS); Activities of Daily Living assessed with the Disability Assessment for Dementia (ADL DAD); Dementia Quality of Life Measure (DEMQOL); EQ-5D 5 level (EQ-5D-5L); ICEpop Capability measure for older people aged ≥ 65 (ICECAP-O); Neuropsychiatric Inventory Questionnaire (NPI-Q); Client Service Receipt Inventory (CSRI); Telephone Montreal Cognitive Assessment (T-MoCA); patient medical records review; patient serious adverse events (SAEs). We will conduct Process Evaluation interviews and Discrete Choice Experiments to inform refinement of the intervention content and delivery.

**Discussion:**

Our findings will inform the refinement and delivery of a subsequent definitive cRCT that tests the clinical and cost-effectiveness of the TIMES intervention compared with usual care.

**Trial registration:**

This study received approval from the Health Research Authority (HRA) and London–Harrow Research Ethics Committee (Reference: 24/LO/0123), and is sponsored by the University of Exeter (Reference: 2021–22-38). Trial registration: ISRCTN, ISRCTN54051676, registered 20 March 2024, https://www.isrctn.com/ISRCTN54051676.

## Introduction

In the UK, there are 850,000 people living with dementia (PLWD); 700,000 family carers of PLWD; and 2.4 million people living with mild cognitive impairment (MCI) [1–6]. Sleep disturbance, the increased number and duration of awakenings and increased percentage of light sleep, is common in PLWD (20–90%) and MCI (18.3–45.5%) [7–13], and has a significant impact on their day-to-day living [14–18] and family carers [19–27]. Poor management of sleep disturbance in PLWD/MCI also affects health and social care systems, due to an increase in complications from comorbidities, earlier admission to care homes, and an increased cost of healthcare [28–31].

Primary healthcare management of sleep disturbance in PLWD/MCI is difficult, as it often requires addressing multiple interacting factors (Table 1) and is rarely self-reported by PLWD/MCI [48]. PLWD/MCI and carers often request, and General Practitioners (GPs) often prescribe, licensed sleep medications, including sedative or hypnotic medications such as benzodiazepines or z-drugs [48–50]; however, there is no evidence that sedative medications are effective in the medium to long term [50, 51], and the use of hypnotics has been associated with increased incidence of fractures and strokes in PLWD [52, 53]. Cumulative sedative burden can also lead to increased daytime drowsiness and sleep disruption, which PLWD/MCI are at greater risk of developing [54–56].

**Table 1 Tab1:** Multifactorial, interacting, causes of sleep disturbance in PLWD/MCI

Age-related changes, e.g. lower sleep efficiency, weakening of circadian entrainment, visual impairment, contributing to sleep–wake rhythm abnormalities [32]
Psychological disorders e.g. stress, anxiety or depression [33, 34]
Medicine side effects e.g. Donepezil (medicine licensed for dementia) and nightmares [35]
Co-morbidities e.g. arthritis, heart failure, reflux and obstructive sleep apnea [36]
Environmental factors e.g. excessive nocturnal noise or light, low daytime light exposure, uncomfortable room temperature, and nocturnal care practices [37, 38]
Activity levels e.g. reduced physical activities, social disengagement and daytime napping [39–46] Wider social determinants of health [47], including expectations and perceptions of normal sleep and de-medicalisation agenda

Non-pharmacological approaches to understand and manage sleep problems may provide alternatives to medications. Cognitive behavioral therapy for insomnia (CBT-I) is typically recommended as the first-line treatment for chronic insomnia in adults (including patients with comorbidities), and may be provided as a multicomponent treatment that includes several therapeutic strategies, such as psychoeducation (sleep hygiene) and sleep-restriction therapy [57, 58]. However, access to these treatments can be limited, and there is little evidence that supports the effective use of non-pharmacological interventions for sleep problems in PLWD [59]. Although a recent study involving a multicomponent intervention has shown improvements in the sleep of PLWD in their home, which remained beyond intervention delivery and can be implemented with minimal clinical training [60, 61].

Ideal management of sleep disturbance may be constrained by the reality of available options, for example, if medication is relied on when other non-pharmacological approaches have been tried and failed, or are not available [57, 59, 62, 63]. In weighing up the pros and cons of different sleep management approaches, clinicians must also review and manage co-morbidities that contribute to sleep disturbance, including associated medications. Patients and clinicians may then face a difficult compromise in dealing with side-effects from medications that also offer important benefits [64]. Successful management of sleep disturbance in PLWD/MCI therefore requires whole-person attention to multiple interacting contributory components, with goals and priorities of care varying both between and within individuals over time. This may be achieved by negotiating tailored sleep-management plans to meet individual needs and circumstances.

## Aims and objectives

The TIMES intervention has been co-designed, with input from PLWD/MCI, carers with lived experience, and healthcare professionals, to improve wellbeing in PLWD/MCI and carers by delivering person-centred (i.e. tailored) care that optimises sleep. This study aims to assess the feasibility and acceptability of conducting a definitive cRCT that tests the clinical and cost-effectiveness of the TIMES intervention. To achieve this, we will use quantitative and qualitative approaches to examine participant engagement, recruitment rates, retention to the trial, completeness of outcome data, intervention fidelity, and operational procedures. Additionally, we will explore the facilitators and barriers to patient recruitment to inform future trial implementation.

### Co-primary objectives

#### Objective A

Co-primary objectives are to assess the (1) feasibility (% of eligible people consenting to the study) and (2) acceptability (% of intervention participants completing all three stages of the intervention) of conducting a definitive cRCT of the TIMES intervention for PLWD/MCI, and their carers, who experience sleep disturbance.

### Secondary objectives

#### Objective B

To assess the ability to collect data to address putative primary and secondary outcomes for the definitive cRCT.

#### Objective C

To assess the ability to collect data to assess the cost-effectiveness and resource use for the definitive cRCT.

#### Objective D

To inform iterative refinement of the TIMES intervention for the definitive cRCT.

## Methods

### Design

This study is a multi-centre, two-arm, single-blinded, cluster-randomised (by site) controlled feasibility trial of the TIMES intervention. Patient participants in primary care (PLWD/MCI, with problematic sleep disturbance) and their carers (family members, friends or spouses, or paid professional carers, such as care home staff) will be recruited in pairs (dyads).

Participant dyads recruited by sites (GP practices) that are cluster-randomised to the intervention group will be offered the TIMES intervention; participant pairs recruited by sites that are cluster-randomised to the control group will receive treatment as usual (standard care). Participant recruitment commenced in September 2024. All participants will be invited to complete baseline assessments and follow-up assessments at 9- and 15 weeks, from the date of their baseline assessment (Fig. 1). No long-term follow-up is planned.

**Fig. 1 Fig1:**
[figure not shown]
Study schema

Participants and healthcare professionals from both treatment groups will be asked to engage in an optional process evaluation interview and Discrete Choice Experiment (DCE) survey to inform an iterative revision of the intervention for a definitive cRCT.

### Screening and recruitment

We aim to recruit 64 patient–carer dyads from 10 cluster-randomised GP practices in England, UK (Intervention group = 32 dyads, Control group = 32 dyads). Potential participants will be identified from primary care practices and include patients who are diagnosed with dementia or MCI and experience sleep disturbances that are considered problematic by the person with dementia, their family, professional or family carer, or clinician. Efforts will be made through discussions with National Institute of Health and Care Research (NIHR) Regional Research Delivery Networks (RRDNs) and GP practices during site selection and recruitment to promote diversity of the participant sample, e.g. for ethnicity, socioeconomic background, and geographic location (rural/urban).

Potentially eligible patients will be identified and recruited by site staff, mail-out, text messages, emails, phone calls, and during routine consultations. Pending GP consent, patients may also be approached via a third-party data processing platform ECLIPSE (Electronic Checking Leading to Improved Prescribing/Treatment Safety & Efficiency), by text message or phone call, to ascertain expressions of interest in participating in the study. ECLIPSE is a nationally accredited NHS provider that securely manages health data for the NHS (https://www.eclipselive.org/).

Potentially eligible patient and carer participants, and consultees where applicable, will be provided with a Participant Information Sheet containing a lay summary of the study and details on how to access further information about the study. Potential patient participants must have a family carer or professional carer (i.e. care home staff). Carers will be screened and recruited to the study as a pair (dyad) with the patient participant. A blinded Research Nurse will screen potential patient and carer participants, following inclusion/exclusion criteria, and if eligible, invite them to participate in the study. Potential participants that meet the inclusion criteria will be invited to provide informed consent and enrol in the study. If the patient participant lacks capacity, a consultee will be asked to provide a favourable opinion on their behalf. A professional consultee may not also act as a carer-participant for the same dyad. Participants have the right to withdraw at any time during the study without prejudice to their care. In addition, a patient participant may be withdrawn in good faith at the request of their carer, healthcare professional, or consultee, if they feel it is within the best interest of the patient, e.g. if a patient participant shows signs of distress from participating in the study.

### Inclusion criteria

Patient participants (PLWD/MCI)Aged > 18 yearsClinical diagnosis of dementia/MCI of any subtype and stageIn primary care and registered with a participating general practiceResiding at home or in a community care home in EnglandHas sleep problems of any type that are considered problematic by the PLWD/MCI, their family or carer. Have a family or professional carer who provides support at least 1 h per week and is willing to solely assist with the completion of outcomesAble to communicate in English sufficiently well to complete the outcome measures and questionnaires. Has capacity to provide informed consent or has a personal or professional consultee who is able to provide favourable opinion on behalf of the PLWD/MCI

Carer participantsAged > 18 yearsResides in EnglandAble to communicate in English sufficiently well to complete the outcome measures and questionnaires. Has capacity to provide informed consentHas lived or professional experience of sleep disturbance of the PLWD/MCI for whom they provide careIs not already enrolled in the study with another patient participant (each carer participant can only take part once)

### Exclusion criteria

Patient participants (PLWD/MCI)Deemed overburdened or has severe unstable (mental or physical) health problems (as determined by the Research Nurse or GP where appropriate)Unable to communicate even with augmentative and alternative communication supportDoes not have a family or professional carerUndergoing end-of-life carePlanned unavailability for > 3 weeks during intervention and follow-up

Carer participantsDeemed overburdened or has severe unstable (mental or physical) health problems (as determined by the research nurse or GP where appropriate)Diagnosis or health condition that may impair their ability to complete outcome assessments, as determined by the carerPlanned unavailability for > 3 weeks during intervention and follow-up

## Intervention

The TIMES intervention is a clinical assessment and management support tool, in which a tailored care plan is co-created by the patient–carer dyad and GP, subsequently reviewed by the GP, and (if necessary) revised by the patient–carer dyad and GP. While the overall intervention is a novel package—comprising GP Training, Assessment in Context (SADL), a Co-Created Tailored Plan consultation, and a Review and Revise consultation (see below)—the individual components of this complex intervention are familiar to GPs and may be delivered as part of usual care.

The intervention is comprised of the following three elements:I.Assessment in context: patient participants will be asked to complete a one-off Sleep-related Activities of Daily Living (SADL) pre-consultation assessment. The SADL will explore and capture holistic social, health, and healthcare domains, which are associated with disruption to daily living and may be associated with problematic sleep disturbance in PLWD/MCI. The SADL will be completed after the Baseline Assessment and before the first consultation. The SADL will be used by the GP to co-create the tailored plan. Patient participants will be invited to complete the SADL in their home or care home with support from the carer participant.II.Co-create tailored plan: a planned/pre-booked extended face-to-face consultation (30 min) between a General Practitioner (GP; not nurse practitioner), who has received Advanced Generalist intervention training relevant to the delivery of primary care in England (see below), and the patient–carer dyad will be held, to explore and improve sleep-related disruptions to daily living. This consultation should take place within 3 weeks (+ 1 week) after the Baseline Assessment is completed and review information captured in the SADL, and will occur at the participant’s GP practice, home, or care home.The GP will use information from (i) the SADL, (ii) the patient’s clinical record, and (iii) current guidance/best practice on condition management to inform the care planning process (using the intervention training video), alongside the discussion with the patient–carer dyad, to develop a co-created tailored care-plan for the PLWD/MCI that addresses factors affecting their sleep disturbance and its impact on their carer. The consultation will draw on best practice in Advanced Generalist Medicine. Outputs will include a written explanation of problems, intended actions, and anticipated impact of the tailored care plan for PLWD/MCI patients, which will be reviewed 4 weeks later (− 1/+ 2 weeks).III.Review and revise: 4 weeks (–1/+ 2 weeks) after the first consultation, in which the Co-created Tailored Plan was developed, the patient–carer dyad will attend a second, pre-booked, standard in-person consultation (15 min) with their GP or, if appropriate, a relevant healthcare professional delegated by their GP, to review and if necessary revise their Tailored Care Plan. This review will be based on shared observations of whether the intended benefits/outcomes of the Tailored Care Plan have been achieved, the impact of goals and outcomes, and whether any adjustments to improve the effectiveness of the Tailored Care Plan are needed.

### Intervention training

Intervention training for GPs will be provided via pre-recorded video, and take approximately 60 min. The training video will optimise/emphasise the skills of Advanced Generalist Practice, by introducing GPs to a 3Es framework (Engagement, Enhancement, Extension) used in the consultation to co-create the tailored care-plan. Training will also address the known barriers to delivery of tailored care, by offering evidence-informed permission for AGP, and enhanced confidence in the skills and practice of AGP.

### Usual treatment

PLWD/MCI and carer participants in the Control Group will receive treatment as usual, according to appropriate NICE Guidance. This will likely vary according to individual patient needs and GP practices where the PLWD/MCI is treated. Treatment as usual will follow usual care within participating practices, underpinned by standard application of NICE pathway guidelines for dementia: assessment; diagnosis; risk assessment and management; and information [65]. Usual care for PLWD/MCI may involve sleep hygiene advice.

## Data collection

### Randomisation and blinding

#### Randomisation is at the GP practice (site) level

Ten GP practices will be randomised in batches of two sites at once, with the static list’s site number generated by the unblinded Trial Statistician (or delegate). A Trial Manager who is blinded to the static randomisation list will request the Trial Statistician to allocate treatment arms based on the order of site confirmation of capacity and capability. Requests for site confirmation of capacity and capability will be completed simultaneously in blocks of two. Five practices will be allocated to each study arm (1:1 allocation ratio), using a block design (i.e. five blocks of two practices each). Randomisation will not be stratified.

#### This is a single-blinded study

The nature of the intervention does not allow practical blinding for patient and carer participants or for intervention providers (GPs) at any level. However, recruitment, screening and collection of outcomes will be conducted by Research Nurses, who are blinded to participant treatment allocation. All analyses will be conducted by the trial statistician who is blinded to treatment allocation. Any inadvertent unblinding will be reported to an unblinded trial manager through an eCRF report on the EDC system and recorded as a deviation to protocol on an appropriate unblinded log in the Trial Management File.

### Baseline and follow-up assessments

Non-identifiable general demographic data, including age, sex, ethnicity, eligibility (or lack of), and reason for declining consent (if applicable), will be collected on screening logs for all potential participants during screening. Patient medical history, putative outcome measures for the definitive trial, and Serious Adverse Events (SAEs) will be collected at baseline and 9- and 15-week follow-ups (Table 2). All outcome measures are interviewer administered by a blinded Research Nurse, over the phone or in person. Proxy-rated (informant) questionnaires are completed by the professional/family carer participant on behalf of the PLWD/MCI participant. Approximate time to complete outcome assessments at each follow-up is estimated at 50 min for PLWD/MCI; 60 min for Carers. Participants will be informed of their treatment allocation once their baseline assessment is completed. Protocol non-compliances will be reported to an unblinded trial manager through an eCRF report on the EDC system and recorded in the Trial Management File. Any missing data fields will be queried and followed up with site staff, with explanations described in a corresponding non-compliance form. This information will be used to inform outcome selection for a definitive trial.

**Table 2 Tab2:** Planned outcomes for the definitive cRCT in priority order of assessment

Clinical outcomes	Description	Time-point
Sleep Disorders Inventory (SDI) for PLWD/MCI	The putative primary outcome for a definitive trial is sleep in PLWD/MCI at 15 weeks, as assessed using the overall SDI score [66]. This subjective measure has advantages over objective sleep measures in this population, as it can be rapidly assessed during screening and avoids potential acceptability issues associated with wearable or technological devices. The overall SDI score is derived from the multiplication of frequency and severity of items 1–7, and then summed across items 1–7. A score of ≥ 4 [67] or ≥ 5 [68] on any single item (questions 1–7) is considered clinically significant. Higher scores indicate greater sleep disturbance. The SDI quantifies the (i) frequency (5-point scale), (ii) severity (4-point scale), and (iii) carer distress (6-point scale), associated with seven symptoms of sleep-disturbance that may have occurred in the past 2 weeks (see below; question 8 is not rated). It is validated for use as a proxy assessment for PLWD who reside in either domestic or care homes, and has recently been used in studies of non-pharmacological interventions in PLWD [60, 61, 69, 70]. The SDI includes carer-rated questions on whether the PLWD/MCI (1) has difficulty falling asleep; (2) gets up during the night; (3) wanders, paces or gets involved in inappropriate activities at night; (4) awakens the carer during the night; (5) awakens at night, dressing, and planning to go out, thinking that it is morning and time to start the day; (6) awakens too early in the morning; (7) sleeps excessively during the day; and (8) has other night-time behaviours that bother the carer. Approximately 10 min to complete	Baseline, 9 weeks, 15 weeks
Epworth sleepiness scale (ESS) [71]	Eight self-rated questions (scale 0–3) that assess day-time sleeping/dozing behaviour (component score range 0–24; > 10 indicates excessive sleepiness). Approximately 2–3 min to complete	Baseline, 9 weeks, 15 weeks
Activities of Daily Living (ADL): Assessed with the Disability Assessment for Dementia (DAD) [72]	Proxy-rated questionnaire consisting of 40 binary questions on the PLWD/MCI’s ability to perform basic or instrumental ADL’s in the past 2 weeks. Scores are converted to percentage (range: 0–100), with higher scores indicating greater competence in ADL. Approximately 15 min to complete	Baseline, 9 weeks, 15 weeks
Dementia Quality of Life Measure (DEMQOL) [73]	Thirty-one proxy-rated questions or twenty-eight self-rated questions (4-point scale) on quality of life, validated for PLWD at all stages and care arrangements, which can also be used to calculate utility values for estimating QALY [74]. Participants recall their experiences over their past week, including feelings, worries about their memory, everyday life, and overall quality of life. Higher scores indicate better quality of life. An improvement of at least 5/6 points for DEMQOL, and 0.02–0.05 points for DEMQOL-U, is considered clinically meaningful [75]. Approximately 10–15 min to complete	Baseline, 9 weeks, 15 weeks
EQ-5D 5 level (EQ-5D-5L) [76]	Proxy-reported by the carer, and self-rated 5 questions (5-point scale) on: Mobility; Self-care; Usual activities; pain/discomfort; and anxiety/depression. Higher scores indicate greater problems. Utility scores will be used to estimate QALYs for economic analysis. Approximately 2–3 min to complete	Baseline, 9 weeks, 15 weeks
ICEpop Capability measure for older people aged ≥ 65 (ICECAP-O) [77]	Assessment of wellbeing and quality of life in older people (ICECAP-O), with five questions (4-point scale) on: attachment (love and friendship); security (thinking about the future without concern); role (doing things that make you feel valued); enjoyment and pleasure; control (independence). Overall scores are converted into a single-index value with a range of 0–1, with zero indicating no capability (i.e. death) and one indicating full capability. Outputs will also provide an estimation of wellbeing-adjusted life years (WALYs) to inform cost-effectiveness analyses of interventions in social care. ICECAP-A and ICECAP-O instrument items correlate, scores can be calculated from each other with a good confidence, and validity of both instruments has been confirmed in the age groups 50–70 [78]. Approximately 5–10 min to complete	Baseline, 9 weeks, 15 weeks
Neuropsychiatric symptoms: Neuropsychiatric Inventory Questionnaire (NPI-Q) [79]	Twelve proxy-rated questions that assess severity (affect) of neuropsychiatric symptoms to the patient (3-point scale) and distress to the carer (5-point scale). Higher scores indicate greater neuropsychiatric changes that have occurred since the patient first began to experience memory problems. Approximately 5 min to complete	Baseline, 9 weeks, 15 weeks
Client Service Receipt Inventory (CSRI) [80]	Self- and proxy-rated health and social care service-use of the PLWD/MCI in the past 3 months for economic analysis. Questions will include the frequency of resource use in primary, community, social care, loss income from carers, etc. Approximately 10 min to complete	Baseline, 9 weeks, 15 weeks
Telephone Montreal Cognitive Assessment (T-MoCA) Mini—Version 2.1 English (MoCA 5 min/Telephone)	Self-rated non-visual cognitive assessment that can be completed over the phone and is validated for MCI and dementia, (https://mocacognition.com/paper/), assesses auditory attention, mental flexibility, verbal fluency, sentence repetition, word-list memory, and orientation to time and place, with a maximum of 15 points. Lower scores indicate greater cognitive impairment. Approximately 5 min to complete	Baseline, 9 weeks, 15 weeks

TIMES is a pragmatic intervention that has been designed to be delivered in routine clinical practice, in which a review consultation occurs at monthly intervals while modifications to intervention components are reassessed. The 15-week follow-up endpoint is therefore intended to capture relatively short-term effects.

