### Health economic analysis

We will describe mean costs and mean effects, presenting disaggregated costs and consequences. Methods will be designed for capturing: (i) the resources required to deliver the intervention; (ii) health, social and wider care service resource use; (iii) health economic outcomes relating to HRQoL and capability wellbeing. These findings will inform the development of future economic evaluation to be undertaken alongside the definitive cRCT to: (i) establish the resources required to provide the intervention, (ii) estimate intervention costs, and (iii) conduct a full cost-economic analysis (CEA). The intervention costing and CEA, based on within-trial data collection, will be undertaken against a primary perspective of the NHS/Social Care, with participants and broader societal perspectives considered in sensitivity analyses. The future CEA will synthesise cost and outcome data to present an incremental cost-effectiveness ratio (ICER) for the primary economic endpoint of policy relevance, including cost per quality-adjusted life-year (QALY).

Descriptive statistics will be presented for dementia-specific HSVs and wellbeing values at each assessment point (mean, standard deviation, range) and for QALYs and WALYs over the 15-week follow-up period, calculated using the standard AUC approach. We will use an intention-to-treat analysis, taking the previously mentioned NHS and social care perspective. No subgroup analysis will be conducted as this is a feasibility trial and not powered for inferential analyses. As this is a feasibility trial, we will report descriptive data only for each trial arm, with confidence intervals for between-group comparisons. No *p*-values will be reported. Primary analysis will be based on complete case data, in which each individual analysis will be based on observed (i.e. not imputed) data from participants with completed fields that are required for each respective analysis. Losses to follow-up at data collection points will be presented for both primary and secondary outcomes. Missing outcome data will also be discussed, along with its causes. Outputs from the feasibility study will follow CHEERS reporting conventions [89].

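### A fixed 3-month CSRI recall at 9 and 15 weeks does not fit the visit schedule, so neither follow-up form, nor their sum, gives service use for the 15 weeks over which QALYs are calculated

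*Protocol article*

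**What the plan says.** In Table 2 (section Baseline and follow-up assessments), the CSRI row gives a single recall period: "health and social care service-use of the PLWD/MCI in the past 3 months for economic analysis". Its time-point column reads "Baseline, 9 weeks, 15 weeks", with no different recall for the follow-up visits. The Design section sets "follow-up assessments at 9- and 15 weeks, from the date of their baseline assessment", so week 0 is the baseline assessment for everyone.

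The Health economic analysis section will report "QALYs and WALYs over the 15-week follow-up period, calculated using the standard AUC approach". On the cost side it says "We will describe mean costs and mean effects, presenting disaggregated costs and consequences", and among the items to be captured it lists "health, social and wider care service resource use". The article gives no rule for combining or reconciling CSRI reports from different visits.

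**The concern.** A fixed recall works for instruments that describe a current state, such as the SDI (past 2 weeks) or the DEMQOL (past week). The CSRI is different because it feeds a cumulative quantity: service use and cost over a period. For that, the recall periods of successive forms should join end to end and together cover the follow-up. A 3-month recall applied at visits 9 and 6 weeks apart cannot do this.

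Objective C asks whether data can be collected to assess cost-effectiveness and resource use in the definitive trial, where the intended economic outcome is cost per QALY. If the CSRI periods do not match the QALY period, costs and effects refer to different stretches of time. The completeness criterion in Table 4 would not reveal this, because every form could be returned in full and a cost for weeks 0 to 15 would still not be available.

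**Working it through.** **Inputs**
- Recall length w: 3 months (Table 2, CSRI row). Assumption: 13 weeks, since 365.25/4/7 = 13.04. Range checked: 12 weeks (3 × 4) to 13.14 weeks (92 days).
- Visits at weeks 0, 9 and 15 from baseline (Design; Table 2), assumed to fall on schedule.
- Effect period: weeks 0 to 15 (Health economic analysis).

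The article states no figure of its own on this point, so there is none to reproduce.

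**Periods covered.** A form completed at week t covers t - w to t. With w = 13:
- Baseline form: weeks -13 to 0.
- 9-week form: 9 - 13 = -4, so weeks -4 to 9.
- 15-week form: 15 - 13 = 2, so weeks 2 to 15.

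**Consequences**
- Pre-baseline part of the 9-week form: w - 9 = 4 weeks; 4/13 = 31%. These weeks are also on the baseline form.
- Overlap of the two follow-up forms: 9 - (15 - w) = w - 6 = 7 weeks (weeks 2 to 9).
- Recall on the two follow-up forms together: 2w = 26 weeks. This is 15 weeks of follow-up, plus 7 weeks reported twice, plus 4 weeks before baseline. If summed, 26/15 = 1.73, or 73% over at a constant rate of use. Counting only post-baseline time, (26 - 4)/15 = 22/15 = 1.47.
- 15-week form alone: it misses 15 - w = 2 weeks; 2/15 = 13% of follow-up.
- Calendar time touched by the two follow-up forms: 26 - 7 = 19 weeks (weeks -4 to 15), not 15.

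**Sensitivity to the length of 3 months**

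| | w = 12 | w = 13 | w = 13.14 |
|---|---|---|---|
| Pre-baseline on 9-week form (weeks) | 3 | 4 | 4.1 |
| As share of that form | 25% | 31% | 32% |
| Overlap of follow-up forms (weeks) | 6 | 7 | 7.1 |
| Sum of recall (weeks) | 24 | 26 | 26.3 |
| Sum / 15 | 1.60 | 1.73 | 1.75 |
| Gap, 15-week form alone (weeks) | 3 | 2 | 1.9 |

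Under every reading, neither form and no sum of the two matches weeks 0 to 15.

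**Could another fixed recall make the two forms join?** No. Reaching back from week 9 to baseline needs w of at least 9, while avoiding overlap between weeks 9 and 15 needs w of at most 6. The recall has to differ by visit.

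**With recall since the previous assessment.** The forms cover weeks 0 to 9 and 9 to 15: 9 + 6 = 15 weeks, with no overlap, no gap and no pre-baseline time.

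**The case against.** The strongest reply is that overlapping questions do no harm until someone adds the answers, and the article does not say that anyone will. Presenting disaggregated costs is compatible with reporting each assessment separately. That stands. A reader might infer that costs will be double-counted by 73%, but the documents do not support this as a fact; the figure applies only if the two follow-up forms are summed. What is certain is that 7 weeks are asked about at both visits. Not summing still leaves the 15-week form about 2 weeks short.

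Three other strong readings also go beyond the documents:
- *That the missing first 2 weeks hide the cost of the intervention.* The first consultation may fall within 3 weeks (+1 week) of baseline, and no distribution is given. The resources needed to deliver the intervention are listed separately from service use. What is missing from the 15-week form is other service use in those weeks.
- *That pre-baseline use biases the comparison of arms.* With practices randomised, and recruitment not differing by arm, use before baseline has the same expectation in both. It raises each arm's cost level and adds noise, but does not shift the expected absolute difference.
- *That distorted cost parameters will be carried into the definitive trial.* Table 3 measures Objective C by the proportion of participants who stay in and provide valid data, which the recall period does not bias. The parameters it names for revising the sample size concern the proposed primary outcome and possible key secondary outcomes; cost SDs are not named.

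Finally, the article condenses an unpublished protocol, and the form itself may word the follow-up recall differently. If so, Table 2 misdescribes it. As printed, the recall is 3 months at all three visits.

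**Conclusion.** The point holds as a mismatch between a stated recall period and a stated schedule. About 4 of the 13 weeks on the 9-week form precede baseline, the follow-up forms overlap by about 7 weeks, and neither form nor their sum yields service use for the 15 weeks over which QALYs and WALYs are calculated. The size of any cost error depends on an analysis choice the article leaves open: 73% over if the forms are summed at a constant rate of use, or 13% of follow-up missing if only the 15-week form is used.

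This rests on reading 3 months as about 13 weeks (the conclusion is the same from 12 to 13.14), on visits falling on schedule, and on Table 2 describing the form in use. Severity is moderate: costs here are descriptive, no effectiveness conclusion depends on them, and the full cost-effectiveness analysis belongs to the later trial. It still deserves correction, because testing whether resource-use data can be collected is a stated objective.

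**What to change.** Keep the 3-month recall at baseline. At 9 weeks ask about use 'since your baseline assessment', and at 15 weeks 'since your 9-week assessment'. Because recall lengths then differ, compare baseline with follow-up as weekly rates (baseline total over 13 weeks, follow-up total over 9 + 6 = 15).

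Recruitment began in September 2024, with 8 months planned for recruitment, delivery and data collection, so many or all forms may already be complete. For those, state in the health-economic analysis that the 9- and 15-week reports are not added together, and label the 15-week costs as covering about weeks 2 to 15 wherever they appear beside 15-week QALYs or WALYs. Carry the corrected recall into the definitive trial's CSRI. If the form in use already has a shorter follow-up recall, correct the description in Table 2 instead.

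The cost is a wording change on one form and a short analysis rule. The price of the change is that baseline and follow-up totals are no longer directly comparable, which the weekly rates address.
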